### Dual-energy X-ray absorptiometry

Total body fat mass and total bone-free lean mass will be acquired by total body scans using Dual-energy X-ray absorptiometry (DXA) using standardised protocols [115, 116]. Appendicular lean mass will be derived from the sum of lean mass in both upper and lower extremities.

### Bioimpedance analysis

Bioelectrical impedance analysis (BIA) is a method for measuring body composition, including muscle mass, body fat, and total body water. Alternating low and high-frequency electrical currents are sent through the water in the body via contact with electrodes to measure impedance. This is a well-known and tested method for body mass and muscular health assessment. Multi-frequency BIA (mfBIA) equipment (InBody S10, InBody Co., Ltd., Seoul, KR) makes it possible to assess a particular muscle as a whole, as well as looking at a muscle at the fiber level [117].

### Sample size

An overall sample size of 300 patients was defined according feasibility.

However, according with the primary endpoint and the study design, the statistical power estimation was performed.

More specifically, we simulated the width from the lower limit of 95% confidence intervals for the Ratio Between Two Proportions.

The following parameters and assumptions were included into the equation:overall sample size of 300 patients;assumption of the balanced numbers (1:1) of physically frail sarcopenic [3 ≥ SPPB score ≤ 8] and healthy active elderly [SPPB score > 8] individuals;assumption of the unbalanced numbers (2:1) of individuals with and without sleep disorders at the baseline;expected rate of 9% of SPPB score < 9 at 12 months in healthy active elderly individuals [SPPB score > 8] without sleep disorders [118–123];expected rate of 27% of inability to complete a 400 m walk test in less than 15 min (without sitting, stopping for more than one minute, receiving help, or using a walker) in physically frail sarcopenic elderly individuals [3 ≥ SPPB score ≤ 8] without sleep disorders [18];an overall risk ratio of 1.55 at 12 months for individuals with sleep disorders versus the ones without sleep disorders (pooled expected rate 18%);an alpha error of 5%;

Thus, to reject the null hypothesis the lower limits of the ratio must not be lower than 1.11 (corresponding to a 20% of the lower limit of the differences).

Participants will be enrolled at the Frail elderly lab of the Geriatric Clinic Unit within the Interagency integrated activity department of continuity and multicomplexity of the University Hospital of Parma, by acquisition of informed consent and if, upon the geriatric multidimensional assessment, the eligibility criteria given in this study protocol will be met.

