## Abstract

**Background:**

Sarcopenia, altered bone and systemic metabolism, physical frailty and cognitive decline are age-dependent and interrelated phenomena. Sleep disorders which are erroneously considered as part of the aging process might be the unifying underlying mechanism of accelerated aging. It is well-known that impaired sleep health could predict neurodegeneration and functional decline. However, in current clinical practice, sleep disorders are not routinely screened and only a minority of cases require second-tier specialist techniques. The delay of their assessment, without a comprehensive evaluation, results in higher healthcare costs. The aim of SOMNUS-DARE project is to detect, in a translational manner, the role of sleep disorders in the genesis of physical frailty, sarcopenia, mild cognitive impairment, and to measure their contribution to the progression of these phenomena towards mobility-disability and dementia.

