**Fig. 7 Fig7:**
[figure not shown]
SOMNUS-DARE analytic aspects

It will be measured in terms of SPPB score < 9 [51, 52] for healthy active elderly individuals and in terms of inability to complete a 400 m walk test in less than 15 min (without sitting, stopping for more than one minute, receiving help, or using a walker) [53] for physically frail sarcopenic elderly Individuals.

The secondary and exploratory outcomes have already been listed in Table 1.

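### As stated in the article, the primary comparison is one overall risk ratio across two different transitions, so on its own it does not inform the aim on the genesis of physical frailty

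*Protocol article*

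**What the plan says.** The Abstract gives the project two linked aims: "the role of sleep disorders in the genesis of physical frailty, sarcopenia, mild cognitive impairment, and to measure their contribution to the progression" of these conditions towards mobility disability and dementia. The Discussion repeats both. Under Objectives, the primary objective is narrower: the effect of sleep disorders on incident physical and functional worsening from baseline to 12 months.

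Under Outcomes, worsening is defined by baseline group. "It will be measured in terms of SPPB score < 9 [51, 52] for healthy active elderly individuals"; for physically frail sarcopenic individuals it is failure to complete a 400 m walk within 15 minutes. The first event is an onset, the second a progression.

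Under Sample size, the rates without sleep disorders are kept apart, "expected rate of 9% of SPPB score < 9 at 12 months in healthy active elderly individuals" and "expected rate of 27% of inability to complete a 400 m walk test in less than 15 min" in the frail group. They are then merged into a pooled 18% and "an overall risk ratio of 1.55 at 12 months for individuals with sleep disorders versus the ones without sleep disorders". No risk ratio by group is given. Statistical methods refers back to the sample size estimation and names Clopper-Pearson intervals and a test for two proportions, with multivariable logistic regression for interpretation. It names no stratification by baseline group, no primary estimate by group and no interaction. Healthy and frail groups are named there only for the secondary incidences and prevalences and for mortality.

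**The concern.** Genesis and progression are separate questions, and each group's primary event answers only one of them. A single ratio averages the two effects, with weights set by the event rates. The frail group has three times the planned unexposed rate of the healthy group (27% against 9%) and so dominates the average.

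What is at stake is interpretation. If the overall ratio came out near 1.55, a reader could take it to apply to healthy and frail people alike, although the same figure would arise with no effect at all in healthy people. In the other direction, a real effect confined to healthy people would hardly move the overall ratio.

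**Working it through.** **Inputs, all from Sample size.** Total 300; frail to healthy 1:1, so 150 each; with to without sleep disorders 2:1, so 200 and 100; unexposed 12-month rates 9% (healthy) and 27% (frail); overall risk ratio (RR) 1.55. *Assumption:* the 2:1 split holds within each group (100 exposed, 50 unexposed), because the article gives it only overall.

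**The plan's own figure.** 0.5 × 9% + 0.5 × 27% = 18%. The stated pooled rate reproduces as the rate without sleep disorders. The exposed rate is then 1.55 × 18% = 27.9%.

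**Expected events at a common RR of 1.55**

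| Group | Exposed | Unexposed | Total |
|---|---|---|---|
| Healthy | 100 × 0.1395 = 13.95 | 50 × 0.09 = 4.5 | 18.45 |
| Frail | 100 × 0.4185 = 41.85 | 50 × 0.27 = 13.5 | 55.35 |

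Frail share = 55.35 / 73.8 = 75%.

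**Weights in the overall ratio.** With equal groups and equal exposure splits,

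overall RR = [9/(9 + 27)] × RR(healthy) + [27/(9 + 27)] × RR(frail) = 0.25 × RR(healthy) + 0.75 × RR(frail).

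**Different effects, same overall 1.55**

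- No effect in healthy people: RR(frail) = (1.55 − 0.25)/0.75 = 1.73. Frail events 13.5 + 46.8 = 60.3, a share of 60.3/73.8 = 82%.
- No effect in frail people: RR(healthy) = (1.55 − 0.75)/0.25 = 3.2. Frail events 13.5 + 27 = 40.5, a share of 40.5/73.8 = 55%.

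In 200,000 simulated trials the unstratified 95% CI excluded 1 in 43.4% with a common RR of 1.55 and in 43.6% with 1.00 in healthy and 1.73 in frail people. The pooled test does not distinguish these cases.

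**An effect of 1.55 in healthy people only.** Overall RR = 0.25 × 1.55 + 0.75 = 1.14, with power of about 5% to 7%.

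**Precision by group at RR 1.55.** SE(log RR) = √[(1 − p1)/(n1·p1) + (1 − p0)/(n0·p0)].

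- Healthy: √(0.8605/13.95 + 0.91/4.5) = 0.514; 95% CI 0.57 to 4.24; power about 12% (two-sided 5%).
- Frail: √(0.5815/41.85 + 0.73/13.5) = 0.261; 95% CI 0.93 to 2.58; power about 42%.
- Interaction (log of the ratio of RRs): √(0.514² + 0.261²) ≈ 0.58.

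For scale, the healthy group alone would need about 1,497 people (499 + 998) for 80% power.

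**If exposure is not balanced across groups (assumed figures).** Suppose there is no effect at all, but 120 of 150 frail and 80 of 150 healthy people have sleep disorders. Exposed risk = (80 × 0.09 + 120 × 0.27)/200 = 19.8%; unexposed = (70 × 0.09 + 30 × 0.27)/100 = 14.4%; crude RR = 1.38. This is why the overall estimate should itself be stratified.

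**The case against.** The strongest reply is that the overall ratio fits the primary objective as written. Worsening defined by baseline state is a legitimate single outcome, and the genesis wording is a project-level aim that the article never ties to the primary test alone. This stands: the overall ratio is not an error.

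Other planned analyses also bear on onset. Table 1 lists incident sarcopenia and pre-frailty conditions; Statistical methods adds an ordinal model for single-unit SPPB decline and repeated-measures models to 24 months. This stands too, although none of these is stated as the primary effect by group.

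A reader might infer that the study will never look at the groups separately, or that a positive result could not support the genesis aim at all. The article supports neither reading. It does not exclude estimates by group, Fig. 7 on analytic aspects is not shown, and a fuller protocol or analysis plan may contain them. Nor does the article say that the pooled result would be reported as an effect in healthy people, and no figure in it suggests that the 1.00 and 1.73 split is likely.

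Lastly, the added estimates will be imprecise. In the 1.00 and 1.73 case the interaction has an SE of about 0.61 against a log difference of 0.55, or about 15% power. That is a reason to present it as an estimate with its CI, not a reason to leave it out.

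**Conclusion.** The point holds as a limit on interpretation. What the article fixes for the primary outcome is one overall ratio and one two-proportion test, and that result is about the same with or without an effect in healthy people. By itself it does not inform the genesis aim; it bears mainly on progression, with some support on onset from the secondary outcomes and the ordinal SPPB model.

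The 0.25 and 0.75 weights rest on equal groups and the same 2:1 exposure split in each. The 75% event share also needs a common RR; it runs from about 55% to 82% when the effect is confined to one group and the overall ratio is still 1.55. The pooled test remains usable for the primary objective. How it will be read should be settled before outcome data are seen.

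**What to change.** In Statistical methods:

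- Stratify the overall estimate by baseline SPPB group, for example by Mantel-Haenszel. This guards against unequal exposure across groups but does not separate the two effects, hence the next item.
- Beside it, report the primary risk ratio with 95% CI separately for healthy (onset) and frail (progression) people.
- Report the interaction between baseline group and sleep disorder on the ratio scale, as an estimate with CI, and state that non-significance will not be read as equal effects.

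In the interpretation text, state in advance that the healthy-group 12-month estimate is descriptive (expected 95% CI about 0.57 to 4.24, power about 12%) and that the pooled primary result will not by itself be used to claim an effect on the genesis of frailty.

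This takes a few sentences and uses only data already planned, with no extra participants. The downside is that the wide healthy-group interval will be visible.

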Our methodological choices, incorporating both subjective and objective measures, as recently recommended by the American Heart Association [128], could comprehensively assess sleep health dimensions and minimize measurement bias. Furthermore, age-adapted analytic procedures we are planning to adopt, could account for interindividual differences and age-related changes in sleep physiology, as highlighted by recent methodological reviews [126].

Anticipated challenges include participant attrition, adherence to sleep monitoring protocols, and potential confounding from comorbidities, psychosocial factors, and medication use. On the other hand, regular follow-up, use of user-friendly wearable devices, robust statistical adjustment for covariates, and optimized sampling frequency represent countermeasures we are planning to involve and which allow to capture sleep variability, and not to miss key biological relationships as well [129, 130].

The project will allow to analyse sleep disorders, a public health problem, in the older population, where it is extremely relevant condition not fully addressed. In particular, reliance on subjective sleep assessment through questionnaires in cognitively frail individuals is known to introduce reporting bias, which can lead to under- or overestimation of sleep disturbances. On the other hand, objective sleep assessment through devices like actigraphs, sleep profilers, and cardio-respiratory monitors can mitigate this bias by providing quantifiable sleep parameters. Therefore, the inclusion of both types of measures, in research and clinical protocols, is known to represent the best opportunity to ensure robust and clinically meaningful assessment of sleep in vulnerable populations, as each provides distinct information: subjective measures reflect perceived sleep quality, while objective measures correlate more closely with sleep architecture. This approach will allow us to assess the sleep misperception, a relevant aspect of sleep health in this population [131–133].

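### The lower limit of 1.11 does not follow from the plan's own inputs: with 300 participants and a risk ratio of 1.55 the expected 95% lower limit is about 0.96, and a limit of 1.11 would be reached in about one cohort in four

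*Protocol article*

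**What the plan says.** All of the following comes from the Sample size section of the Protocol article, except where noted.

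- Size: "An overall sample size of 300 patients was defined according feasibility". The section then says that a power estimation was nevertheless done, by simulating the lower limit of the 95% confidence interval for a ratio of two proportions.
- Strata: "assumption of the balanced numbers (1:1) of physically frail sarcopenic" and healthy active individuals.
- Exposure: "assumption of the unbalanced numbers (2:1) of individuals with and without sleep disorders at the baseline".
- Rates without sleep disorders: "expected rate of 9% of SPPB score < 9 at 12 months in healthy active elderly individuals", and "expected rate of 27% of inability to complete a 400 m walk test in less than 15 min" in the frail sarcopenic stratum.
- Effect: "an overall risk ratio of 1.55 at 12 months for individuals with sleep disorders versus the ones without sleep disorders (pooled expected rate 18" per cent). Alpha is 5%.
- Conclusion, introduced as following from these inputs: "to reject the null hypothesis the lower limits of the ratio must not be lower than 1.11". A bracket ties this figure to 20% of a lower limit of differences, without further definition.

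No power percentage and no allowance for dropout is given. The Discussion says: "Anticipated challenges include participant attrition". The Statistical methods section refers back to the sample size estimation when it introduces the confidence intervals and the test for two proportions.

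**The concern.** A lower limit of 1.11, set at the end of a list of inputs for 300 participants, suggests a study that can comfortably exclude a ratio of 1 at the planned effect. If the inputs lead to a limit below 1, the planned effect would more likely than not fail to reach significance. A null result could then be taken as evidence against an effect of sleep disorders, when the cohort was too small to tell.

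The role of 1.11 is also unclear. It could be the limit expected from the design or a margin that the observed limit must clear. These call for different corrections, and the second would change the hypothesis being tested.

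**Working it through.** **Inputs (Sample size section).** N = 300 at 2:1, so n1 = 200 with and n0 = 100 without sleep disorders. Unexposed risk p0 = (9% + 27%)/2 = 18%, which matches the stated pooled rate. Exposed risk p1 = 1.55 × 0.18 = 0.279. Two-sided 95% interval, z = 1.96.

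**Attempt to reproduce 1.11.** Log-scale interval for a ratio of two proportions:

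SE(log RR) = √[(1 − p1)/(n1·p1) + (1 − p0)/(n0·p0)] = √[0.721/55.8 + 0.82/18] = 0.2418

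Lower limit = exp(ln 1.55 − 1.96 × 0.2418) = 0.965

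Upper limit = exp(ln 1.55 + 1.96 × 0.2418) = 2.490

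The stated figure is not reproduced. Other readings at N = 300 and RR 1.55 also miss it:

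| Reading | Expected lower limit |
|---|---|
| Log interval, 2:1, 18% in the unexposed | 0.965 |
| Score interval | 0.982 |
| Mantel-Haenszel over the two strata | 0.980 |
| Inverse-variance over the two strata | 0.983 |
| 18% taken as the whole-cohort rate | 0.874 |
| Exposure ratio reversed (1:2) | 1.006 |
| Exposure 1:1 | 1.011 |
| One-sided 95% limit | 1.041 (1.05-1.06 with score or stratified methods) |

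**Size at which the expected limit is 1.11.** At 2:1, SE² = k/N with k = 0.721/(⅔ × 0.279) + 0.82/(⅓ × 0.18) = 17.54. The SE needed is ln(1.55/1.11)/1.96 = 0.1704, so N = 17.54/0.1704² ≈ 604. At 400:200 the limit is 1.109. An expected limit of exactly 1 needs about 351, but that corresponds to only about 50% power. For 80% power the same formula, with 1.96 + 0.84 in place of 1.96, gives about 717 for a limit above 1 and about 1,235 for a limit of at least 1.11.

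**If 1.11 is a threshold.** With 18% observed in the unexposed, the observed ratio must be about 1.77 for the lower limit to reach 1.11 at 200:100. With the true ratio at 1.55, summing over all binomial outcomes gives:

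- lower limit above 1: 43.8%;
- two-sided 5% test for two proportions (pooled variance) significant: 46.9%;
- lower limit at least 1.11: 25.6%.

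Simulating the two strata separately gives 43.6% for the first and 24.9% for the last.

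**Detectable ratio.** At a true ratio of 1.85 the same summation gives 79.3% for a lower limit above 1 and 81.5% for the test for two proportions. So 80% power falls at about 1.85.

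**Attrition.** The document gives no rate. With an assumed 15% loss (170:85), SE = 0.2418/√0.85 = 0.2623 and the interval is 0.93 to 2.59. Power at 1.55 falls to about 37-41%.

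**The case against.** **The text gives a threshold, not an expected result.** This stands as a reading. The sentence says what the limit must be in order to reject; it does not say that 300 participants are expected to give 1.11. The bracket could fit a chosen margin, since 1 + 0.20 × (1.55 − 1) = 1.11, though that origin is a guess. So is a calculation run by mistake at 600, where the limit is 1.109. A reader might infer that the protocol promises a lower limit of 1.11; the wording makes this plausible but does not state it. The threshold reading does not rescue the paragraph, because the threshold would then be met only about one time in four.

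**The study could still reach 1.11.** True. It would be too strong to say that 300 participants cannot deliver it: by chance about a quarter of cohorts would.

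**The size was set by feasibility and no power level is claimed.** This is correct and legitimate, and it is why the size itself is not challenged. It does not cover a figure presented as following from inputs that do not yield it.

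**The Study design section mentions an interim reassessment of power.** It is linked to study duration, with no stated rule and no stated increase in size, so it does not repair the figure.

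**The planned confidence intervals would show the imprecision.** That reduces the risk of misreading a null result but does not remove it, since the stated rejection rule is itself unclear.

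**Conclusion.** The point holds. On the plan's own inputs the expected 95% interval at N = 300 is about 0.96 to 2.49, and no reading tried at that size and confidence level gives 1.11. As an expected limit, 1.11 is wrong and would need about 600 evaluable participants. As a decision rule, it has about a 25% chance of success when every assumption is true, and it replaces the usual null of 1 with a stricter one that is not explained. Power against a ratio of 1 is about 44-47% at 1.55 and reaches about 80% only near 1.85.

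These figures assume that all 300 are evaluable, that exposure splits exactly 2:1, that 18% is the risk in those without sleep disorders, and that the 5% alpha is two-sided. The document does not state the sidedness; two-sided is taken from the 95% interval. The 15% loss is an assumption used for illustration only.

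**What to change.** Keep N = 300 on feasibility grounds and replace the 1.11 sentence in the Sample size section. Suggested wording:

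> With 200 participants with and 100 without sleep disorders, an 18% risk in the latter and a risk ratio of 1.55, the expected 95% confidence interval is about 0.96 to 2.49. Power against a ratio of 1 (two-sided 5%) is about 44-47%, depending on the method; about 80% power is reached at a true ratio of about 1.85. The null hypothesis is rejected if the lower 95% limit exceeds 1.

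If 1.11 is meant as a deliberate margin, say so, justify it, and state that the chance of meeting it at a true ratio of 1.55 is about 25%. In either case remove or define the bracket about 20%.

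Add the same figures for the evaluable number after the attrition that the investigators expect. As an example, an assumed 15% loss gives an expected lower limit of about 0.93.

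The cost is one paragraph of protocol text and a less favourable stated precision. The number of participants and the study procedures do not change.

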### Data collection and management

Data collection will be carried out using the REDCap (Research Electronic Data Capture, Vanderbilt University, Nashville, TN, US) platform installed at the University Hospital of Parma, according to the operating instructions released by the Clinical and Epidemiological Research Unit of the University Hospital of Parma. A specific computerized data collection form (eCRF) will be prepared. The system will be accessible exclusively to authorized personnel specifically profiled (data entry operator, monitor, data analyst, etc.) by entering strictly personal credentials (user name and encrypted password). Quality of data will be guaranteed through automated controls active during the data entry process (pre-calculated fields, branching logic, self-validations) and during the data management procedures (deletion, display and filtering). A “Data Validation Program” will be defined in order to detail which data will be checked (validated) and to define the quality monitoring indicators aimed at verifying completeness (missing data) and the presence of deviations (non-adherence to the protocol). The system will also be able to record the log of accesses and all operations performed (Logging and Audit Trail). The eCRF will respect the principle of minimization, i.e. the inclusion of the collection of data strictly necessary for the purposes of the main and secondary objectives of the study, and will be made available for possible verification by designated representatives in the event of monitoring visits.

